## Objectives and outcome measures/endpoints

### Primary objective

To assess the population PK of IV, IM and oral TXA solution in pregnant women.

### Secondary objectives

•To assess the effect of the three routes of TXA administration on D-dimer concentration in blood samples.•To assess the concentration of TXA that crosses the placenta into the neonate via the three routes of administration.•To assess clearance of any TXA in neonate.•To assess the safety of the three routes of TXA administration.•To assess the effect of the three routes of TXA administration on postpartum bleeding.

### Primary endpoint

Blood TXA concentrations over time in pregnant women.

### Secondary endpoints

•Blood concentrations of D-dimer over time•TXA concentration in umbilical cord and neonate after birth•Local reactions at IM injection sites•Adverse events (maternal and neonate)•Neonate status Apgar score•Measured blood loss from start of CS to 2 hours after•Clinical diagnosis of PPH

## Trial design

A prospective, randomised, open label study to be conducted in obstetric units in Pakistan and Zambia. Potential eligible participants will undergo CS. Consent will be obtained as per section “Methods for informing and obtaining consent”.

## Trial setting

Participants will be recruited from obstetric units in Pakistan and Zambia. Recruitment, treatment and follow-up will be conducted at the recruiting obstetric units. Names of participating sites will be listed on the
trial website.

## Participant eligibility criteria

### Inclusion criteria

•Women admitted to hospital giving birth by CS•History of at least one risk factor for PPH•Adult (≥18 years old)

### Exclusion criteria

•Women giving birth vaginally•Women with a known allergy to TXA or its excipients•Women with current antepartum haemorrhage•Women known to have received TXA within 48 hours prior to randomisation•Women with known renal impairment•Women with any known blood clotting disorder

## Trial procedures

### Summary of trial procedures

The trial overview flow-chart is shown in
Figure 1 the summary of trial procedures is shown in
Figure 2. The protocol has been prepared according to the Standard Protocol Items: Recommendations for Interventional Trials (SPIRIT) 2013 guidelines
^
48
^ (Additional files 1 and 2,
*Extended data*)
^
49
^. The complete copy of the protocol can be found in Additional file 3 (see
*Extended data*)
^
49
^.

**Figure 1. f1:**
[figure not shown]
Trial overview.

**Figure 2. f2:**
[figure not shown]
Summary of trial procedures.

### Screening of potential participants

Potential eligibility will be assessed by a clinician at the participating obstetric clinic when the woman is admitted for a CS.

### Methods for informing and obtaining consent

**
*Information giving.*
** Women who are admitted for a CS with one risk factor for PPH will be given oral and written information and fully informed consent will be obtained by the clinician. If she is unable to read or write, the information sheet will be read to her, and she will mark the consent form with a cross or thumbprint. In this case, an impartial witness must be present throughout the procedure and provide a signature confirming the mark.

The clinician will explain the trial to the woman verbally in a language that she understands and provide a written participant information sheet (Additional file 4,
*Extended data*)
^
49
^. In brief, it will be explained that she will receive the usual care given to women having a CS at the hospital. The clinician will explain that if she accepts to participate, because she is at risk of increased post-partum bleeding she will receive a drug called tranexamic acid into a vein, or a muscle, or to swallow it, or she may receive no trial drug. We need to study this because injecting TXA into a muscle or swallowing it are easier than injecting it into a vein.

This would mean that the treatment could help many more women giving birth who are at a high risk of bleeding. The clinician will explain to the woman the expected risks of the treatment to herself and the baby. If the woman objects to inclusion, her views will be respected. The clinician will explain to the woman that she has the right to withdraw from the trial at any time, without the need to justify the reason and without any consequences on the care provided to her and her baby. An overview of the consent procedure is provided in Additional file 5 (see
*Extended data*)
^
49
^.

**
*Documenting consent process.*
** In all cases, the clinician obtaining consent should record in the participant’s medical notes the method used for obtaining a participant’s consent. The clinician should retain the original signed and dated consent form, a copy should be given to the woman.

### Baseline data collection

Baseline parameters will be used to build a PK model that describes the TXA concentration in the blood over time following TXA administration. 

The following baseline data will be recorded:

•Demographic (age) and anthropometric data (height and weight [body mass index and body surface area using the Du Bois formula will be derived]). Information on these parameters can be collected at baseline•Medical and pregnancy history•PPH risk factor(s)•CS planned date and time•Reason for CS•Vital signs including blood pressure, temperature, heart rate, and respiratory rate•Full blood count•Blood test to assess renal function (urea, creatinine, estimated glomerular filtration rate)•Any foetal abnormalities•Any foetal distress

### Randomisation

After collecting baseline data, enrolled participants will be randomised into one of the four groups described in “Description of investigational product and justification of the dosage, route of administration, administration schedule and treatment duration”. The sequence for each dosing cohort will be created using computer-generated random numbers, using blocking to ensure the required balance in the allocation of participants to treatment arms. The allocation ratio will be 1:1:1:1. 

An IT coding expert supported by a statistician who are not involved in the conduct of the trial will prepare the randomisation codes. Eligibility will be confirmed and randomisation done via an online database. Once the code is generated, the trial intervention will be prepared and administered by a trained trial team member. Participants and all trial staff will be blind to treatment allocation until randomisation is completed.

### TXA administration and timing of biological samples

The time of the TXA administration is T
_0_. One blood sample will be taken for PK prior to drug administration.

Post TXA administration blood samples will be taken at different time points during 24 h as per the schedules in
Figure 3. We understand that the care of the participant takes priority over the sampling schema and that sample times will inevitably differ from those indicated. If it is not possible to obtain a sample at the scheduled time, the sample should be collected as soon as feasible with the exact time of collection recorded. Reasons for any delay will be recorded. Where there are less than six evaluable PK samples obtained after TXA administration from a participant, this participant will be replaced in the study.

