### Description of investigational product and justification of the dosage, route of administration, administration schedule and treatment duration

In this study, women will be randomised to four groups:

1.
**IV TXA GROUP:** 30 women will receive 1 g of TXA by IV route. IV TXA treatment rapidly achieves the plasma levels of TXA needed to inhibit fibrinolysis and prevent excessive bleeding. Pharmacological research has shown that an IV dose of 1 g TXA maintains therapeutic plasma levels for around 3 hours, the period when the risk of bleeding is greatest
^
12,
19
^. However, the TXA PK and PD in pregnant women has not been described so far.2.
**IM TXA GROUP:** 30 women will receive 1 g of TXA by IM route. Studies of IM TXA in healthy volunteers report good absorption and no adverse effects
^
11,
12
^. The dose will be given as two 5 mL (0.5 g each) injections into the thigh (rectus femoris or vastus lateralis) or buttocks (gluteal muscles) muscles, depending on a clinical assessment of muscle mass
^
12
^. The 1 g dose (10 mL) is divided to reduce the volume injected (5 mL is considered the upper limit)
^
20
^. The injections will be given using the most appropriate needle size for IM administration from the sites stock (1" between 19 - 25 gauge and from 1 ½ inches up to 3" for large adults) using the Z-track method to seal the medication in the muscle
^
20
^.3.
**TXA SOLUTION ORALLY:** 30 women will receive 4 g of TXA oral solution. The dose was selected because of the 50% oral bioavailability and because previous and preliminary PK data show that the absorption through the oral route is much slower than through the IV or IM routes, with much lower maximal concentration (Cmax)
^
12,
13,
19,
21
^. Therefore, higher doses are needed to reach therapeutic levels, according to simulations. The oral route (tablets or solutions) is well characterised
^
22–
24
^, but oral TXA PK and PD in pregnant women have not been described so far.4.
**NO TXA CONTROL:** 30 women will receive no TXA and will be the control group for PD, blood loss and safety data.

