**Figure 3. f3:**
[figure not shown]
Timing of biological samples.

*Pharmacokinetics*: Finger prick blood samples (2 × 10 µL per sample) for TXA quantitation will be taken as per
Figure 3.

*Pharmacodynamics*: Blood samples (3 mL of venous blood in tubes containing 3.2% sodium citrate) for D-dimer quantitation will be taken as per
Figure 3.

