### Collection and storage of biological samples

Only one blood sample for PK analysis will be collected at baseline for women who are randomised to receiving no TXA. Samples for D-dimer, full blood count (FBC) and renal function will be collected.

Maternal blood will be taken from a cannula to avoid multiple venepuncture as follows:

Two samples of 3mL each will be taken for FBC and two samples of 3mL each for renal function. Blood samples will be collected in purple top EDTA tubes for FBC and yellow top tubes with separation gel and clot activator for renal function.

Five samples for D-dimer of 3 mL for each sample of blood to be taken in collection blue top tubes containing 3.2% sodium citrate. Blood samples for D-dimer, FBC, and renal function will be collected from the hospitals and analysed by a local central laboratory. The laboratory will be asked to store the sample used for D-dimer analysis until the end of trial to allow for repeat tests if needed. In the event of failure of any of the PK samples, this will be used as a back-up and will be destroyed at the end of the trial.

Each maternal PK sample require about 20 µL of blood taken using a Mitra
^®^ cartridge from a finger prick (2 × 10 µL samples taken on the 2 cartridges of the same device to have one primary and one confirmation sample if needed). Sites will be provided with written procedures on how to obtain the blood sample using the Mitra
^®^ cartridge. Cartridges will be labelled with the date and time the sample was taken and with the participant Study Identification number.

The total volume of blood taken (less than 35 mL) should have no clinical impact on the participant.

To obtain the umbilical PK blood sample, once the umbilical cord is clamped, it is wiped with antiseptic and a syringe and needle is inserted into the vein in the umbilical cord to withdraw a small amount of blood. PK samples from the umbilical cord and neonates will also be taken using the Mitra
^®^ cartridge system as described above.

A blood sample from the neonate (2×10 µL) will be taken using the Mitra
^®^ cartridge at the time of the routine clinical heel prick test to avoid additional heel pricks.

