### Premature exit of trial participant

Participants may exit the study at any time and for any reason. A previously given consent can be withdrawn. The investigator can withdraw a participant from the trial for any safety reason or if it is in the participant's best interest.

If a participant exits the trial prematurely or withdraws consent or refuses consent for continuation, data collected up to time of premature exit will be used. Participants who withdraw from the trial with less than six post treatment PK samples will be replaced to ensure the four intervention groups remain balanced.

**
*Monitoring participants after the premature termination of treatment.*
** In case of an adverse event to the participant or her baby, the investigator will complete an adverse event report and monitor the event until the end of her participation in the research or until it has resolved or reached a stable state.

**
*Procedure for replacing participants.*
** If consent procedures are complete but the TXA dose is not given in full, the participant will be replaced.

When oral TXA is given and the participant vomits within the first hour of receiving the intervention, this participant will be replaced in the study. However, data collection for the participant will continue to the trial end.

Where the CS is delayed and takes place more than 2 hours after the administration of the intervention, the participant will be replaced in the study. However, data collection for the participant will continue to the trial end.

If a participant receives the TXA dose but there are less than six post treatment evaluable PK samples obtained after TXA administration, this participant will be replaced in the study. However, data collection for the participant will continue to the trial end.

Data collected from the replaced participants will be used.

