**Placenta transfer and neonate heel prick PK levels:** Concentrations will be presented in tabular form with mean, median, standard deviation and range as appropriate. For each time point, comparisons across groups will be done using the analysis of variance. We will adjust for time between drug administration and sampling. Where both an umbilical cord and neonate heel prick sample is available, these will be used to build a PK model with gestational age and birth weight as the main covariates.

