### Pharmacodynamic analysis

**D-dimer:** Descriptive statistics for D-dimer concentration in maternal blood will be presented in tabular form with mean, median, standard deviation and range (minimum and maximum) as appropriate. For each time point, comparisons across groups will be done using the analysis of variance. The PK data will be combined, and analyses may be conducted to determine a relationship between exposure and the effect on D-dimers.

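### T0 has no stated equivalent in the no-TXA control arm, and the per-time-point D-dimer ANOVA takes no account of actual sampling time or of delivery

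*Protocol article*

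**What the plan says.** Under TXA administration and timing of biological samples, the article states "The time of the TXA administration is T" (subscript 0), and then "Post TXA administration blood samples will be taken at different time points during 24 h as per the schedules in" Figure 3. The same section accepts that real sample times will depart from schedule and asks for the exact time to be recorded.

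D-dimer draws have their own pointer to that figure: venous samples "for D-dimer quantitation will be taken as per" Figure 3. Collection and storage of biological samples gives the number: "Five samples for D-dimer of 3 mL for each sample of blood". The figure is not available here.

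The control arm is described as follows: "30 women will receive no TXA and will be the control group for PD, blood loss and safety data". It gives D-dimer samples but only a baseline PK sample. Description of trial population places its no-treatment allocation about an hour ahead of the caesarean. No other starting event is named for it.

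Under Procedure for replacing participants, a woman is replaced "Where the CS is delayed and takes place more than 2 hours after the administration of the intervention". That section closes by saying that data from replaced women will be used.

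The Pharmacodynamic analysis reads: "For each time point, comparisons across groups will be done using the analysis of variance". It mentions neither sampling time nor delivery. The paragraph on placental transfer and neonatal levels, by contrast, adds: "We will adjust for time between drug administration and sampling".

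**The concern.** A clock that starts at dosing suits pharmacokinetics. D-dimer can be expected to respond to surgery and birth as well as to the drug, so for this endpoint the distance of a sample from delivery matters too. Two gaps follow from the text.

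First, the arm against which every TXA route is judged on D-dimer has no stated moment that plays the part of T0. A site must decide for itself when that woman's schedule begins.

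Second, the stated analysis treats all samples with the same label as equivalent. Yet the interval from T0 to caesarean is approximate by design, and women delayed past 2 hours stay in the data. An early sample may be before birth in one woman and after it in another.

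D-dimer is the only pharmacodynamic marker among the listed endpoints, and the no-TXA arm is the only untreated comparator. At stake is how cleanly the early D-dimer contrasts can be read.

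**Working it through.** The plan gives no figure on this point to reproduce: the sample size rests on the precision of PK parameters, with no D-dimer effect or SD. The checks below show size under stated assumptions.

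**1. Distance of a sample from birth.** Distance = sample time after T0 minus birth time after T0. The only nominal times in the text are the PK ones (Sample size calculation), so they serve as an illustration; the five D-dimer times may differ. Birth at 0.5 to 2 h after T0 is assumed, with 3 h for a delayed woman whose data are kept.

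| Sample after T0 | Birth at 0.5 h | 1 h | 2 h | 3 h |
|---|---|---|---|---|
| 1 h | +0.5 | 0 | −1 | −2 |
| 2 h | +1.5 | +1 | 0 | −1 |
| 4 h | +3.5 | +3 | +2 | +1 |
| 24 h | +23.5 | +23 | +22 | +21 |

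At 1 and 2 h the sign can change between women. At 24 h the spread is small against the elapsed time.

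**2. Noise under a common origin.** Suppose D-dimer changes by s SD per hour from birth, and birth is uniform over 0.5 to 2 h. The variance of birth time is 1.5²/12 = 0.1875 h², so the outcome variance is multiplied by 1 + 0.1875 s²:

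- s = 0.25: 1.012
- s = 0.5: 1.047
- s = 1: 1.188, which makes 30 women worth about 30/1.188 = 25

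A simulated one-way ANOVA (4 arms of 30, 5% level, no drug effect, 4,000 runs) gave false-positive rates of 4.6%, 5.1% and 4.8% for these three slopes. A common origin therefore costs precision, not validity.

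**3. Bias if the control origin differs.** The same simulation with the control clock displaced (the F test ignores direction):

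| Slope (SD/h) | 0.25 h offset | 0.5 h | 1 h |
|---|---|---|---|
| 0.25 | 5.2% | 7.5% | 14.3% |
| 0.5 | 6.6% | 13.3% | 45.0% |
| 1 | 12.9% | 40.8% | 96.2% |

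**4. Direction and size on the D-dimer scale.** If control samples are taken earlier while D-dimer is rising, the control mean is too low. For a rise by a factor F over 120 minutes and an offset of d minutes, the relative reduction is 1 − F^(−d/120):

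| Assumed rise over 2 h | 10 min | 20 min | 40 min |
|---|---|---|---|
| 1.5-fold | 3.3% | 6.5% | 12.6% |
| 2-fold | 5.6% | 10.9% | 20.6% |
| 3-fold | 8.7% | 16.7% | 30.7% |

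A control mean that is too low would mask a reduction by TXA. These figures apply only to draws inside the assumed rise. The slopes, rises and offsets are all assumptions; the document gives no D-dimer course.

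**The case against.** The strongest reply is that the D-dimer schedule is in Figure 3, which cannot be seen. There are five D-dimer draws against nine PK times, so the two schedules differ, and the figure could tie draws to delivery or give the control arm an origin. This stands. A reader might infer that D-dimer times are known to run from TXA and to disregard birth; the documents do not establish that.

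The control arm is also not wholly unanchored, since its allocation is placed about an hour before the caesarean and the planned caesarean time is baseline data. This stands too, although an approximate interval is not a recorded moment. A reader might suppose that sites start the control clock at randomisation, which would make the samples early. Nothing in the text says so.

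Birth timing is partly controlled through the planned one-hour gap and the 2-hour replacement rule. Randomisation should balance the gap on average across arms that share an origin. Both points are right, though keeping replaced women's data means the rule does not cap the gap.

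The cord and neonatal paragraph is not a precedent for a birth-time term, because it adjusts for time since dosing. It shows only that a timing adjustment was thought worth stating there.

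Finally, a control-arm origin and ANOVA covariates might be left to the full protocol or SAP. That is fair for the origin alone. The article does, however, state the D-dimer comparison, and a later analysis document cannot recover a control-arm time that was never recorded.

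**Conclusion.** The point holds in a limited form. The text defines T0 by an event that the PD control arm does not have, and it fixes a D-dimer comparison that ignores actual sampling time and delivery, although both are expected to vary.

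With a common origin the consequence is extra noise in the early, peri-delivery comparisons: a variance increase of about 1% to 19% under the assumed slopes and birth times, and little effect at 24 hours. Systematic bias needs a control clock that starts at a different step. That is possible on this text but not shown. If it happened with control samples early, control D-dimer in the rising phase would read about 3% to 31% low over the assumed range.

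It would be too strong to conclude that the D-dimer results will be biased, or that the trial's main aim is threatened. D-dimer is a secondary endpoint, the article also allows an exposure-response analysis of it, and the primary PK analysis uses actual sampling times.

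**What to change.** Two changes are enough.

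- In TXA administration and timing of biological samples, define a T0 equivalent for the no-TXA arm: a recorded time set at the same step as dosing in the other arms. If Figure 3 already does this, say so in the text.
- In Pharmacodynamic analysis, base the D-dimer comparison on actual sampling times and add to the model at each time point a term for time from birth to sample (negative before birth), or at least a before/after-birth indicator where draws straddle delivery. This recovers precision and also guards against the birth-related part of any origin offset.

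The cost is one recorded time in the control arm and one model term, with no extra samples. Sampling times are already to be recorded; time of birth is assumed to be available from delivery records. The statistical drawback is adjustment for a time that arises after randomisation. This is acceptable if TXA does not affect when birth occurs, which seems reasonable for a caesarean but should be stated.

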**Figure 3. f3:**
[figure not shown]
Timing of biological samples.

*Pharmacokinetics*: Finger prick blood samples (2 × 10 µL per sample) for TXA quantitation will be taken as per
Figure 3.

*Pharmacodynamics*: Blood samples (3 mL of venous blood in tubes containing 3.2% sodium citrate) for D-dimer quantitation will be taken as per
Figure 3.

### Collection and storage of biological samples

Only one blood sample for PK analysis will be collected at baseline for women who are randomised to receiving no TXA. Samples for D-dimer, full blood count (FBC) and renal function will be collected.

Maternal blood will be taken from a cannula to avoid multiple venepuncture as follows:

Two samples of 3mL each will be taken for FBC and two samples of 3mL each for renal function. Blood samples will be collected in purple top EDTA tubes for FBC and yellow top tubes with separation gel and clot activator for renal function.

Five samples for D-dimer of 3 mL for each sample of blood to be taken in collection blue top tubes containing 3.2% sodium citrate. Blood samples for D-dimer, FBC, and renal function will be collected from the hospitals and analysed by a local central laboratory. The laboratory will be asked to store the sample used for D-dimer analysis until the end of trial to allow for repeat tests if needed. In the event of failure of any of the PK samples, this will be used as a back-up and will be destroyed at the end of the trial.

Each maternal PK sample require about 20 µL of blood taken using a Mitra
^®^ cartridge from a finger prick (2 × 10 µL samples taken on the 2 cartridges of the same device to have one primary and one confirmation sample if needed). Sites will be provided with written procedures on how to obtain the blood sample using the Mitra
^®^ cartridge. Cartridges will be labelled with the date and time the sample was taken and with the participant Study Identification number.

The total volume of blood taken (less than 35 mL) should have no clinical impact on the participant.

To obtain the umbilical PK blood sample, once the umbilical cord is clamped, it is wiped with antiseptic and a syringe and needle is inserted into the vein in the umbilical cord to withdraw a small amount of blood. PK samples from the umbilical cord and neonates will also be taken using the Mitra
^®^ cartridge system as described above.

A blood sample from the neonate (2×10 µL) will be taken using the Mitra
^®^ cartridge at the time of the routine clinical heel prick test to avoid additional heel pricks.

PK samples will be placed into suitable sealed biological sample shipping bags and sent weekly to [name] laboratory at UFR Simone Veil - Santé, University Versailles Saint Quentin ([name]) for PK analysis. No participant identifiable data will be transferred to the laboratory. Once all analyses for this trial have been completed, all blood samples will be destroyed.

